### Allocation Concealment and Blinding

A computer-generated, permuted-block randomization sequence were applied for allocation with two block sizes. The patients are randomized to the control group or receive exercise training group in a 1:1 ratio (stratification by sex). The sequence is concealed in an opaque envelope until the intervention is assigned. Patients cannot be blinded to the outcome of randomization, Furthermore, to increase the robustness of the outcomes, outcome assessors are blinded to the outcome of randomization.

### Sample Size Calculation

For CMR-based RVSV, no individual patient data are available. Previously, the REPAIR STUDY demonstrated RVSV from 52.2 ± 17.2 mL to 64.9 ± 19.0 mL (mean ± SD) after 3–5 months under PAH-specific drugs (23). The change from baseline in approximate RVSV was ~9 mL, in line with the literature suggesting that a difference of 8–12 mL is clinically relevant (24). Assuming a standard deviation of 18–22 mL, also based on the hemodynamics sub-study of SERAPHIN, the minimum sample size was 77 subjects for each group, for a total of 154 subjects with a statistical power of 90% and two-sides test of *P* < 0.05. Considering the dropout rate of 20%, the planned sample size was 192 subjects, with 96 in each group.

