### Outcomes

#### Primary Efficacy Outcome

The changes of right ventricular stroke volume (RVSV) from baseline to Week 26 are determined by CMR. RVSV indexed for BSA is shown to predict outcome (22). RVSV quantifies blood flow independently of HR. An increase in RVSV reflects favorable, reverse remodeling of the right ventricle (RV) and is expected to reduce PAH symptoms through better oxygenation.

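### At ~9 mL, the only single effect value given, no SD in the stated 18–22 mL range gives 77 per group at 90% power, and the difference and SD behind 77 are not named

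*Protocol article*

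**What the plan says.** All figures are in the Sample Size Calculation section of the protocol article unless another section is named.

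- **Endpoint** (Primary Efficacy Outcome): "The changes of right ventricular stroke volume (RVSV) from baseline to Week 26 are determined by CMR".
- **Source data:** a drug study is cited for "RVSV from 52.2 ± 17.2 mL to 64.9 ± 19.0 mL (mean ± SD) after 3–5 months" on PAH-specific drugs.
- **Effect:** the next sentence says "The change from baseline in approximate RVSV was ~9 mL", and adds "in line with the literature suggesting that a difference of 8–12 mL is clinically relevant".
- **SD and size:** "Assuming a standard deviation of 18–22 mL, also based on the hemodynamics sub-study of SERAPHIN, the minimum sample size was 77 subjects" in each group, 154 in total, for 90% power with a two-sided 5% test.
- **Inflation:** "Considering the dropout rate of 20%, the planned sample size was 192 subjects, with 96 in each group".
- **Allocation** (Allocation Concealment and Blinding): 1:1.
- **Analysis** (Statistical Analysis): ANCOVA of the change in RVSV with baseline RVSV as covariate. The sample size paragraph mentions no correlation and no variance reduction from that covariate.

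The paragraph does not say which single difference and which single SD produced 77. It also does not say whether 18–22 mL is an SD at one time point, an SD of change, or a residual SD.

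**The concern.** A reader who takes the one point value for the effect and the stated SD range cannot get back to 77 per group. Every SD in the range needs more patients, so the claimed 90% power does not hold at that effect unless something unstated, such as a gain from baseline adjustment, makes up the difference.

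This is the power claim for the primary endpoint. If the trial is null, readers will judge the result against a 10% chance of missing the target effect. At 9 mL with 77 evaluable per group and no baseline adjustment, that chance is 13% to 29%.

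The basis of the effect is also unclear. The two cited means do not differ by the amount given in the next sentence, and the paragraph does not say whether ~9 mL is a change within one treated group or a difference between groups. The trial tests a difference between groups in patients whose medication stays unchanged.

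**Working it through.** **Inputs.** Difference 9 mL (only single value), relevant range 8–12 mL, SD 18–22 mL, power 90%, two-sided 5%, 1:1 allocation, 77 evaluable per group, 20% dropout, 96 per group planned.

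**Step 1: can 77 be reproduced at 9 mL?** The normal approximation is n per group = 2 × (1.960 + 1.282)² × SD² / difference². The two-sample t-test value is about one patient higher.

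| SD (mL) | n per group, normal | n per group, t-test |
|---|---|---|
| 18 | 84.1 | 85.0 |
| 20 | 103.8 | 104.7 |
| 22 | 125.6 | 126.5 |

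No SD in the range gives 77. The need is about 85 to 127 per group.

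**Step 2: power at 9 mL (t-test, no covariate).**

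| SD (mL) | 77 per group | 96 per group (no loss) |
|---|---|---|
| 18 | 86.9% | 93% |
| 20 | 79.2% | 87% |
| 22 | 71.3% | 81% |

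**Step 3: what would make 77 right?** With 77 per group, 90% power needs a standardised difference of 0.526 (t-test).

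- At 9 mL this means an SD of at most 9 / 0.526 = 17.1 mL, below the stated range.
- At the stated SDs it means a difference of 0.526 × 18 = 9.5 mL up to 0.526 × 22 = 11.6 mL.
- Pairs inside both printed ranges that give about 77 (t-test n): 9.5 mL with SD 18 (76.4), 10 mL with SD 19 (76.8), 10.5 mL with SD 20 (77.2), 11 mL with SD 21 (77.6).

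**Step 4: spread over the stated ranges.** Power of 77 per group (t-test):

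| Difference (mL) | SD 18 | SD 22 |
|---|---|---|
| 8 | 78% | 61% |
| 9 | 87% | 71% |
| 10 | 93% | 80% |
| 12 | 98% | 92% |

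**Step 5: could ANCOVA supply the gap at 9 mL?** If 18–22 mL is an SD at one time point, the residual SD is SD × √(1 − r²), with r the baseline–Week 26 correlation. Setting this to 17.1 mL gives r = √(1 − (17.1/SD)²), which is about 0.31 at SD 18 and 0.63 at SD 22 (17.12 mL before rounding).

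**Step 6: the cited change.** 64.9 − 52.2 = 12.7 mL, against ~9 mL in the next sentence.

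**Step 7: dropout.** 77 / 0.8 = 96.25, and 96 × 0.8 = 76.8. This agrees with the stated 96 within rounding.

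**The case against.** The strongest reply is that the paragraph never calls 9 mL the design difference. It reports ~9 mL from a cited study and sets it beside a relevant range of 8–12 mL. The pair 10 mL and SD 19 mL takes the midpoint of that range and an SD that is printed in the paragraph and lies inside 18–22 mL, and it gives 77. On this view the calculation may be correct and only under-described. That stands as far as it goes: a reader might infer that 77 has been shown to be a miscalculation, and the document does not support that. It does not rescue the text as written, because no such pair is named and the one value that is given fails at every SD in the range.

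A second reply is that 71–87% assumes an unadjusted test and the full 20% loss, whereas the primary analysis is ANCOVA. This also stands. The range is conditional and should not be read as the power the design will have. However, the sample size paragraph claims no gain from the covariate, and 77 evaluable per group is its own basis.

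Two further readings are tempting and should not be made:

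- A reader might infer that 77 came from 9 mL with the cited study's baseline SD of 17.2 mL. The normal approximation gives 76.8, so 77, but the t-test gives 77.7, so 78, and other pairs fit equally well. The document does not say which was used.
- A reader might take 76.8 against 77 as a shortfall. It is rounding.

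What ~9 mL stands for depends on the cited study, which is not available here. The mismatch with 12.7 mL is therefore something to explain, not proof of which figure is wrong.

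**Conclusion.** The point holds in a limited form. At ~9 mL, the stated 77 per group and 90% power do not follow for any SD from 18 to 22 mL without baseline adjustment: about 85 to 127 per group are needed, and 77 give 87% down to 71%. This rests on a two-sample t-test at two-sided 5%, on 1:1 allocation, and on the stated SD being the one that governs the comparison.

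If another pair inside the printed ranges was used, the figure can be right. The defect is then that the paragraph does not identify its inputs, and its ranges span 61% to 98% power. Either way, the single 90% needs a stated difference and SD behind it. Separately, 12.7 mL and ~9 mL in adjacent sentences must be reconciled.

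**What to change.** Keep 192 patients and reword the sample size paragraph:

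1. Name the one between-group difference for which the trial is powered.
2. Name the one SD used and its type: single time point, change, or residual.
3. State any baseline–Week 26 correlation assumed for the ANCOVA.
4. Restate the power for those inputs.
5. If the target is 9 mL, report 87%, 79% and 71% power at SD 18, 20 and 22 mL with 77 evaluable per group. Add that 90% needs a residual SD of at most about 17.1 mL, which means a correlation of at least about 0.31 at SD 18 or 0.63 at SD 22 if those are single-time SDs.
6. Reconcile the 12.7 mL between the cited means with ~9 mL, and say whether ~9 mL is a within-group change or a between-group difference.

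Items 1 to 3 come first. Printing the 9 mL figures without them could overwrite a correct calculation that was only poorly described. The cost is one paragraph and no extra patients; the stated power may become less favourable.

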### Data Collection and Management

The detailed participant schedule of assessments is presented in Table 1. Demographic characteristics at enrolment, medical history, physical measurements, medication lists, and NT-proBNP are collected via an electronic medical record and interview by trained research nurses and investigators. In order to avoid missing or erroneous data, data are further verified. The research staff have only the authority to read the database.

### Data Management and Monitoring

A trial inspect will be conducted at least once a year to check research progress and protocol compliance (25). The monitoring report will be submitted to the ethics committee and investigators. The audit is available based on the monitoring report. The study did not need predetermined interim analysis. A statistician will analyze the study results.

### Adverse Events

Participants may voluntarily withdraw at any time, or if they experience a serious adverse event (SAE) that is associated with exercise training. All SAEs are discussed with the principal investigator who assesses seriousness and causality. Other adverse events (AEs), defined as any unfavorable and unintended sign, symptom or diseases, are also recorded. AEs are followed up until normalization, recovery or symptoms stabilize.

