### Study Timeline

A diagram timeline is presented in Table 2. Elaborated baseline evaluations are shown in Supplementary Material 3.

**Table 2 T2:** Study timelines overview.

	**Screening**	**Baseline**	**Observation period**		
	****~**0 month**	**0 month**	**Week 12**	**Week 16**	**Preterm termination**
On-site clinic visit		**√**			**√**
Monthly telephone contact			**√**	**√**	**–**
Informed consent	**√**	**–**	**–**	**–**	**–**
Review eligibility criteria	**√**	**√**	**–**	**–**	**√**
Demographics	**√**	**√**	**–**	**–**	**√**
PAH history	**√**	**√**	**–**	**–**	**–**
Medical history	**√**	**√**	**–**	**√**	**√**
Body mass index	**√**	**–**	**–**	**√**	**√**
Physical examination	**√**	**√**	**–**	**√**	**√**
Vital signs	**√**	**√**	**–**	**√**	**√**
6MWD/HHR	**√**	**√**	**–**	**√**	**√**
Borg scores	**√**	**√**	**–**	**√**	**√**
Echocardiography	**√**	**√**	**–**	**√**	**√**
Right heart catherization	**√**				
Pulmonary function test	**√**				
V/Q lung scan	**√**				
CPET	**√**	**√**	**–**	**√**	**√**
WHO functional class	**√**	**√**	**–**	**√**	**√**
Electrocardiogram	**√**	**√**	**–**	**√**	**√**
Chemistry, hematology		**√**		**√**	
NT-proBNP	**–**	**√**		**√**	
Randomization	**√**	**√**	**–**	**–**	**–**
AE monitoring	**√**	**√**	**–**	**√**	**√**
Concomitant medication	**√**	**√**	**–**	**√**	**√**
Omics*	**√**			**√**	**√**

*6MWD, 6-min walk distance; NT-proBNP, N-terminal pro-brain natriuretic peptide; PAH, pulmonary arterial hypertension; V/Q, ventilation-perfusion; WHO, World Health Organization; CPET, cardiopulmonary exercise testing; HHR, heart rate recovery; AE, adverse event. *Omics indicates proteomics, metabolomics and transcriptomics*.

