### Statistical Analysis

Data will be presented as mean (SD), median (interquartile range), and frequency (percentage) available for data characteristics. For comparisons between groups, a *t*-test or rank-sum test will be applied for quantitative variables, while the χ^2^ test or Fisher's exact test for qualitative variables.

Primary and secondary endpoints will be analyzed using the whole population. However, patients who withdrew their consent, patients with severe protocol violations, or patients without the primary endpoint data, will be excluded from the whole population (26). An intention-to-treat analysis will be used to avoid, with inclusion of all available measures, regardless of whether participants completed the intervention, while the safety analysis will be done in the safety analysis population. Primary outcome analysis will be performed by an analysis of covariance (ANCOVA) model. Changes from baseline in RVSV will be analyzed using an ANCOVA with a factor for other PAH-specific therapies (none, background, or initiated at baseline) and a covariate for baseline RVSV. Missing outcomes were imputed as the multiple imputation. For analysis of categorical data, the McNemar–Bowden test will be used. *P* < 0.05 with two-sided test is considered statistically significant. All analyses will be performed with IBM SPSS V20 (IBM Corp., Armonk, NY, USA).

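### A training-specific withdrawal reason, not separated from leaving follow-up, combines with the analysis exclusions to risk differential loss of Week 26 RVSV

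*Protocol article*

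**What the plan says.** **Adverse Events.** The withdrawal rule reads: "Participants may voluntarily withdraw at any time, or if they experience a serious adverse event (SAE) that is associated with exercise training". The judgement on causality is assigned as follows: "All SAEs are discussed with the principal investigator who assesses seriousness and causality".

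**Primary Efficacy Outcome.** "The changes of right ventricular stroke volume (RVSV) from baseline to Week 26 are determined by CMR". The secondary endpoints are also set at 26 weeks.

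**Rehabilitation Program and Table 1.** Training runs for 2 weeks in hospital and 10 weeks at home, 12 weeks in all.

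**Statistical Analysis.** Three statements bear on patients who stop early:
- Exclusion: "patients who withdrew their consent, patients with severe protocol violations, or patients without the primary endpoint data, will be excluded from the whole population".
- Intention to treat: the analysis is to be done "with inclusion of all available measures, regardless of whether participants completed the intervention".
- Missing data: "Missing outcomes were imputed as the multiple imputation".

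**Table 2.** The last scheduled observation column is Week 16. The column headed "Preterm termination" ticks 6MWD, WHO functional class, echocardiography and CPET, and leaves NT-proBNP unticked. CMR has no row at any visit.

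**The concern.** The withdrawal sentence gives two routes. Voluntary withdrawal is open to everyone. The other route depends on an SAE attributed to training, which a control patient is not expected to have. The sentence does not say whether a patient who takes either route stops the programme or leaves the study.

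The distinction matters because training ends at Week 12 and the endpoint is measured at Week 26. A patient who stops training can still be scanned. If withdrawal is read as leaving the study, that scan is not sought, and the exclusion rule removes the patient from the efficacy analysis, either for withdrawn consent or for lack of the endpoint.

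If trained patients with a related SAE do worse on RVSV than other trained patients, removing them raises the training-arm mean with no matching removal built into the control arm. That is bias in the randomised comparison, which an allowance for dropout in the sample size does not correct.

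**Working it through.** **1. How the statements act on one patient.** Take a trained patient who has a related SAE in Week 8 and stops training.

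| Reading | Week 26 CMR | Place in the primary analysis |
|---|---|---|
| Withdrawal means leaving the study; exclusion rule prevails | Not sought | Excluded; nothing is left to impute |
| Withdrawal means leaving the study; imputation prevails | Not sought | Imputed, by a model the article does not describe |
| Withdrawal means stopping training only; ITT statement prevails | Sought | Analysed as randomised |

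Only the third row delivers the stated ITT aim, and the text does not select it. The exclusion rule and the imputation statement cannot both govern the primary endpoint: if everyone without primary data is removed, no primary outcome remains to be imputed. Correcting the Statistical Analysis section alone would move the patient from the first row to the second. It would not recover a scan that was never sought.

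**2. The plan's own figure.** The only figure bearing on outcome loss is the dropout allowance under Sample Size Calculation: 20%, from 77 to 96 per group.
- 77 / (1 − 0.20) = 96.25, stated as 96
- 154 / (1 − 0.20) = 192.5, stated as 192

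This reproduces to within rounding. It applies the same loss to each arm and protects patient numbers only.

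**3. Illustrative size.** Let q be the share of the training arm lost by this route, and D the amount by which their true mean RVSV change falls below that of the patients who stay. If C is the mean among those who stay, the whole-arm mean is (1 − q)C + q(C − D) = C − qD. The completer mean is therefore too high by q × D.

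Both inputs are assumptions. For scale, D is set at one and two times the roughly 9 mL planning change.

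| q | Patients of 96 | D = 9 mL | D = 18 mL |
|---|---|---|---|
| 2% | 1.9 | 0.18 mL | 0.36 mL |
| 5% | 4.8 | 0.45 mL | 0.90 mL |
| 10% | 9.6 | 0.90 mL | 1.80 mL |

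Against 9 mL, the range for 5–10% loss is 0.45/9 = 5% to 1.8/9 = 20%.

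**4. Effect on the test if training had no effect.** Take SD 18 mL (the lower end of the stated 18–22 mL), 96 controls, 96(1 − q) trained patients and no other loss. The standard error is 18 × √(1/96 + 1/[96(1 − q)]), which is 2.63 mL at q = 5% and 2.67 mL at q = 10%. Shifting the test statistic by qD/SE gives two-sided rejection rates, against a nominal 5%, of:
- q = 5%: 5.3% (D = 9) to 6.3% (D = 18)
- q = 10%: 6.3% (D = 9) to 10.3% (D = 18)

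**5. What these figures leave out.** They give no credit for imputation and assume no comparable loss among controls. With control losses the net bias is q_T·D_T − q_C·D_C, which is zero if share and deficit are the same in both arms.

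**The case against.** A reader might infer that outcome loss is one-sided. The article does not support that. Any participant in either arm may leave at any time, and 20% dropout is planned in each. The SAE clause is permissive and adds one named reason to a general freedom to leave. A deteriorating control may leave too. That loss is related to outcome is likewise an inference, since no link is given. What stands is that one named reason is tied to training, so loss is potentially differential.

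A reader might also infer that the early-termination visit fails to collect the endpoints. This is weak. CMR is missing from every column of Table 2, so its absence says nothing specific about early leavers, and detail may lie in Supplementary Material 3. The NT-proBNP cell is blank in a table that mixes blanks and dashes, so typesetting may be the cause. A value at early termination is in any case not a Week 26 endpoint.

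The ITT sentence does separate completing training from contributing data, and imputation could use baseline RVSV and the early-termination measurements that are ticked. It is therefore too strong to say that imputation must treat those who leave as if they had done as well as those who stay. The imputation model may properly sit in a document not shown. But the ITT sentence is contradicted by the exclusion rule in the same paragraph, so it cannot be relied on to settle the matter.

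Finally, an article commonly leaves retention procedures to the full protocol. That would answer a complaint about missing detail. It does not answer one about statements that, followed as written, produce opposite analyses.

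**Conclusion.** The point holds as a risk of differential loss of Week 26 RVSV. It arises from a withdrawal rule that does not separate stopping training from leaving follow-up, together with exclusions that conflict with the ITT and imputation statements. Bias in favour of training is plausible but not documented: it requires that trained patients who leave after a related SAE do worse than those who stay, and that controls are not lost to a similar degree.

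The 0.45–1.8 mL range (5–20% of 9 mL) rests wholly on the assumed 5–10% loss and 9–18 mL deficit, before any credit for imputation. At 2% loss it would be under 0.4 mL. The article gives no rate with which to narrow this. The wording should be corrected because the remedy is simple and unretrieved scans cannot be recovered at analysis. Nothing here shows that the trial's result will be biased.

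**What to change.** 1. **Adverse Events:** state that ending the training programme does not end study participation. Unless the patient withdraws consent to follow-up, the already planned Week 26 CMR and secondary assessments are sought in both arms.
2. **Statistical Analysis:** reconcile the exclusions with the ITT and imputation statements, so that patients who stop training are analysed as randomised and lack of primary endpoint data is handled as missing data, not as a ground for exclusion.
3. **Table 2:** reconcile the schedule with the Week 26 endpoints. The last column is Week 16 and CMR is not listed. State whether the unticked NT-proBNP cell under early termination is intended.

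The cost is wording, plus some effort to retain patients who have stopped training. No additional CMR at early termination is needed, since the Week 26 assessment is already part of the design. Some patients will still decline follow-up, so the risk is reduced and not removed. The clinical decision to stop training is left as it is.

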### Statistical Analysis

Data will be presented as mean (SD), median (interquartile range), and frequency (percentage) available for data characteristics. For comparisons between groups, a *t*-test or rank-sum test will be applied for quantitative variables, while the χ^2^ test or Fisher's exact test for qualitative variables.

Primary and secondary endpoints will be analyzed using the whole population. However, patients who withdrew their consent, patients with severe protocol violations, or patients without the primary endpoint data, will be excluded from the whole population (26). An intention-to-treat analysis will be used to avoid, with inclusion of all available measures, regardless of whether participants completed the intervention, while the safety analysis will be done in the safety analysis population. Primary outcome analysis will be performed by an analysis of covariance (ANCOVA) model. Changes from baseline in RVSV will be analyzed using an ANCOVA with a factor for other PAH-specific therapies (none, background, or initiated at baseline) and a covariate for baseline RVSV. Missing outcomes were imputed as the multiple imputation. For analysis of categorical data, the McNemar–Bowden test will be used. *P* < 0.05 with two-sided test is considered statistically significant. All analyses will be performed with IBM SPSS V20 (IBM Corp., Armonk, NY, USA).

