#### Secondary Efficacy Outcome

In the same method as that used for the primary endpoints, secondary endpoints are assessed at 26 weeks. They consist of characteristics of the RV, and of widely accepted tools to assess PAH progression:

RV end diastolic volume (RVEDV),RV end systolic volume (RVESV),RV ejection fraction (RVEF),RV mass,WHO FC,6 MWD, andN-terminal pro-B-type Natriuretic peptide (NT-proBNP).

Variables pertaining to the left ventricle (LV) are also assessed.

Changes from baseline to Week 26 in:

LV SV,LV end diastolic volume (LVEDV),LV end systolic volume (LVESV),LV ejection fraction (LVEF),LV mass,RVEDV/LVEDV, andRVESV/LVESV.

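### The stated between-group test for quantitative variables other than RVSV is unadjusted, and the plan does not clearly give the continuous secondary endpoints an ANCOVA on their own baseline, which costs avoidable precision

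*Protocol article*

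**What the plan says.** All references are to the protocol article.

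- **Statistical Analysis, first paragraph.** After a sentence on descriptive presentation comes a general rule for between-group comparisons: a t-"test or rank-sum test will be applied for quantitative variables". It names no endpoint and gives no criterion for choosing between the two tests.
- **Statistical Analysis, second paragraph.** "Primary outcome analysis will be performed by an analysis of covariance (ANCOVA) model". The model is then specified: "Changes from baseline in RVSV will be analyzed using an ANCOVA with a factor for other PAH-specific therapies", with baseline RVSV as covariate. No other endpoint's baseline is mentioned. The significance threshold is P < "0.05 with two-sided test is considered statistically significant".
- **Secondary Efficacy Outcome.** "In the same method as that used for the primary endpoints, secondary endpoints are assessed at 26 weeks". The list that follows holds RVEDV, RVESV, RVEF, RV mass, WHO functional class, 6-minute walk distance (6MWD) and NT-proBNP. A second list of seven left ventricular and ratio measures is headed "Changes from baseline to Week 26 in". The first list has no such heading.

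That makes 13 continuous secondary endpoints (6 + 7); WHO functional class is ordinal.

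**The concern.** Someone applying the Statistical Analysis section literally finds ANCOVA for RVSV and, for every other quantitative comparison, an unadjusted test. That reader would run a t-test or rank-sum test on the 13 continuous secondary endpoints. Baseline values exist for adjustment. Table 2 schedules 6MWD and NT-proBNP at baseline, and a change from baseline in a CMR measure requires a baseline scan.

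The Discussion presents RVEDV, RVESV and RV mass as remodelling endpoints and a strength of the study, and all three are secondary. Unadjusted analysis leaves chance baseline imbalance less well corrected and the intervals wider than they need be. A choice between t-test and rank-sum test with no stated criterion can also be made after the data are seen. For a skewed marker such as NT-proBNP, that choice and the choice of scale can decide the result.

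**Working it through.** **The plan's own figure.** The documents give no power for any secondary endpoint. The only stated size is 77 evaluable per arm for RVSV, at 90% power and two-sided 0.05, with this effect: "The change from baseline in approximate RVSV was ~9 mL". With n = 2(1.960 + 1.282)² × SD²/9², the stated SD range gives 85 (SD 18), 104 (SD 20) and 126 (SD 22) per arm. 77 appears with SD 17.2, the baseline SD quoted in the same section, or with an unstated pair such as 10.5 mL and SD 20. That mismatch is a separate matter. Here 77 serves only as the number per arm.

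**Assumed inputs.** The documents give no baseline to Week 26 correlation (rho), so a range is shown. The SD, σ, is taken as equal at the two times and allocation is 1:1.

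**Variance per patient for the group comparison.**

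- Week 26 value alone: σ²
- Change from baseline: 2(1 − rho)σ²
- ANCOVA on own baseline: (1 − rho²)σ²

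ANCOVA relative to change is therefore (1 − rho²)/[2(1 − rho)] = (1 + rho)/2. The group effect from ANCOVA is the same whether the response is the change or the Week 26 value.

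**Power.** Take an effect that the change-score t-test detects with 80% power, so that effect/SE = 1.960 + 0.842 = 2.802. ANCOVA power is then Φ(2.802/√[(1 + rho)/2] − 1.960).

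| rho | variance ratio | 2.802/√ratio − 1.960 | ANCOVA power | n per arm matching 77 |
|---|---|---|---|---|
| 0.5 | 0.75 | 1.275 | 89.9% | 58 |
| 0.7 | 0.85 | 1.079 | 86.0% | 66 |
| 0.8 | 0.90 | 0.993 | 84.0% | 70 |
| 0.9 | 0.95 | 0.914 | 82.0% | 74 |

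The gain over a change score shrinks as rho rises. If Week 26 values alone were compared, the ratio would be 1 − rho², and 80% would become 89.9%, 97.5% and 99.7% at rho 0.5, 0.7 and 0.8. The documents do not say that this comparison will be made.

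**NT-proBNP.** This was simulated as log-normal with 77 per arm and 4,000 runs per setting. The effect was set so that a t-test on log change has about 80% power. Log-SD and rho are assumptions.

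| log-SD | rho | t, raw change | rank-sum, raw change | t, log change | ANCOVA, log |
|---|---|---|---|---|---|
| 0.8 | 0.5 | 51.2% | 65.8% | 78.8% | 88.7% |
| 0.8 | 0.7 | 52.3% | 64.5% | 79.0% | 84.6% |
| 0.8 | 0.85 | 52.2% | 66.2% | 78.7% | 81.4% |
| 1.2 | 0.5 | 34.9% | 60.6% | 79.3% | 88.6% |
| 1.2 | 0.7 | 32.5% | 61.4% | 79.0% | 84.9% |
| 1.2 | 0.85 | 32.6% | 62.3% | 79.7% | 82.2% |

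Moving from a raw-change t-test to a log-change t-test gains about 27 to 47 points (52.2 to 78.7 at the low end, 32.6 to 79.7 at the high end). Moving from rank-sum on raw change to the log-change t-test gains about 13 to 19 points. Adding the baseline covariate on the log scale gains 2.5 to 9.9 points, much as it would for any endpoint with the same rho.

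**The case against.** The strongest reply is that the t-test sentence was never meant for the secondary endpoints. It stands in the descriptive paragraph beside the χ² and Fisher tests, as a rule for comparing group characteristics would, and endpoint analysis begins in the next paragraph. On that view, the same-method sentence in Secondary Efficacy Outcome carries ANCOVA over to the secondaries and the two sections agree. Details such as covariates and transformations could also wait for an analysis plan that is not shown.

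Part of this stands. A reader might infer that the plan reserves ANCOVA for RVSV and expressly assigns unadjusted tests to everything else. The documents do not say that: the t-test rule names no endpoint, and the same-method wording can be read as analysis.

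It does not remove the point. The same-method sentence sits under Outcomes, speaks of assessment at 26 weeks, and covers WHO functional class, for which ANCOVA is unsuited, so it is a weak specification of a model. Taken literally as one, it imports a model whose only stated baseline covariate is RVSV, which is the wrong covariate for every other endpoint. Nor is this merely silence left to an analysis plan: a test is stated, and it is the less efficient one.

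**Conclusion.** The point holds as a matter of clarity and precision, and is worth correcting. If the Statistical Analysis section is followed as written, the continuous secondary endpoints are tested validly, since randomisation protects the unadjusted comparison, but with avoidable loss. Against a change-score t-test, 80% power would become about 90%, 86% or 84% under ANCOVA at rho 0.5, 0.7 or 0.8. These figures rest on an assumed rho and equal variances at the two times. The primary analysis is untouched.

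Two stronger conclusions might be drawn, and neither is supported:

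- **That baseline values are thrown away.** A change score uses them, only less efficiently. They would be ignored only if Week 26 values were compared alone. The missing change-from-baseline heading on the RV and clinical list leaves that unsettled, but nothing in the text says it.
- **That NT-proBNP suffers most from the lack of baseline adjustment.** The documents give no NT-proBNP distribution. Under the log-normal assumption most of the loss comes from the raw scale, and adjustment accounts for roughly 2 to 10 points.

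**What to change.** In Statistical Analysis, limit the t-test and rank-sum rule to descriptive comparisons and add wording such as:

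*Each continuous secondary endpoint will be analysed as change from baseline to Week 26 by ANCOVA with randomised group and the baseline value of that same endpoint, together with any other factors kept in the primary model. NT-proBNP will be analysed on the log scale and reported as a ratio of geometric means with 95% CI. Rank-based tests will be sensitivity analyses only.*

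In Secondary Efficacy Outcome, define the continuous RV measures, 6MWD and NT-proBNP as changes from baseline, as the LV measures already are, and say whether the same-method sentence refers to measurement or to analysis.

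The cost is a few lines of wording, with no new data and no additional patients.
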